### Patient experience survey

Immediately following the simulation MR scans, participants will be asked to complete a simple, short anonymous survey to assess their experience of each position (see Appendix 1 “Patient Experience Survey”). The survey will ask patients to rate their experience of each of the positions and other common experiences of MRI scans on a Likert scale with an opportunity to explain their rating as free text comments.

This survey has been adapted and developed specifically for this study from a similar tool used by Barnes et al. [15] to investigate the patient experience of treatment on the MRL, as no validated tools were identified in the literature. The survey for this study was critically reviewed by four consumers with radiotherapy treatment experience prior to protocol submission for ethical approval. The survey will be made available to participants on an electronic device at the time of their simulation appointment.

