**Methods:**

Up to 30 patients will be recruited over a 12-month period for participation in this Human Research Ethics Committee approved exploratory cohort study. Patients will be scanned on the magnetic resonance imaging (MRI) Simulator in both the supine and prone positions as per current standard of care for APBI simulation. Supine and prone positioning comparisons will all be assessed on de-identified MRI image pairs, acquired using appropriate software. Patient experience will be explored through completion of a short, anonymous electronic survey. Descriptive statistics will be used for reporting of results with categorical, parametric/non-parametric tests applied (data format dependent). Survey results will be interpreted by comparison of percentage frequencies across the Likert scales. Thematic content analysis will be used to interpret qualitative data from the open-ended survey questions.

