**Discussion:**

The results of this study will be used to assess the feasibility of treating patients with APBI in the prone position on a custom designed board on the MRL. It may also be used to assist with identification of patients who would benefit from this position over supine without the need to perform both scans. Patient experience and technical considerations will be utilised to develop a tool to assist in this process.

*Trial registration* Australian New Zealand Clinical Trials Registry (ANZCTR): ACTRN1262400067583. Registered 28th of May 2024. https://www.anzctr.org.au/ACTRN12624000679583.aspx

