### Study design

This is a prospective, exploratory single-centre pilot study of patients undergoing APBI for early-breast cancer. Patients meeting the American Society for Radiation Oncology (ASTRO) favourable and certain cautionary criteria for APBI will be invited to participate (Table 1) Patients with known contraindications to radiotherapy such as ataxia telangiectasia and systemic sclerosis will be excluded [13]. Participants will be asked to provide written informed consent. Participation will not alter the management of the patients but will inform the decision-making process for the choice of treatment position for future patients treated with ABPI, based on the study outcomes.

**Table 1 Tab1:** ASTRO APBI Favourable and cautionary suitability criteria [13]

Features	
Age	≥ 50 years
Subtype	IDC and DCIS
Size	≤ 3cm
Grade	< 3 (1 or 2)
Margin	Negative ≥ 2 mm
Lymphovascular space invasion	Absent
Hormone (ER) Positivity	Yes
Her2	Negative
Nodal Status	Negative or pN_ITC_

Participants will be scanned on a dedicated Philips Ingenia Ambition MR-RT 1.5T MRI simulator (Koninlijke Philips N.V., Amsterdam, Netherlands) in both the supine and prone positions for APBI as per current departmental standard of care. Assessment of positioning, geometric distortion, patient and breathing motion, and dosimetry will be completed using the de-identified data from these scans. In addition, immediately following the MRI simulation session, participants will be invited to complete a short anonymous electronic survey (using closed and open-ended questions) about their experience of the planning MRI scans (MR specific sensations, information provided about the procedure and positional preferences). CT simulation and treatment will be completed as per standard protocol with appropriate immobilisation equipment in the preferred position (supine or prone as a clinical decision after MR image review) with no further study-based requirements.

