### Positioning assessment

Participants will attend for MRI simulation prior to CT simulation in alignment with standard departmental protocol. For the supine MRI scan, patients will be positioned with both arms up supported by a custom vacuum bag. For the prone MRI scan, patients will be positioned on the Low Procline™ (CDR Systems Inc. Calgary, Canada), which was developed in collaboration with one of our investigators. To make the positional, distortion and breathing motion assessment the standard breast MRI sequences (T1, T2 and Cine imaging) will be acquired in each position, optimised for each laterality. The minimum distance will be calculated between the Target volume and heart, lung(s), skin rind (5mm inside the patient contour), and chest wall.

Participants will be assigned to have either the supine or prone MRI scan first (alternating between the positions) as they are recruited, to reduce bias towards the first or second scan. The order will also be recorded and considered in the analysis of results.

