## Discussion

Access to dedicated MR equipment in a radiation oncology setting, particularly in Australia, is relatively new. Our department is uniquely positioned as the only department in the country with both an MRI simulator and an MRL. Given the scarcity of these resources, it’s important to optimise the utilisation for all patients who would benefit from treatment with this technology. Published research has investigated supine and prone positioning for patients receiving whole breast radiotherapy on conventional linear accelerators (Linacs) with most of these studies utilising CT based simulation imaging for assessment [9, 10, 17]. Some studies with smaller sample sizes [8, 12, 18, 19] have evaluated positional aspects of treatment on the MRL for APBI, but have not explored geometric distortion, breathing motion, positional assessment, dose distribution and the patient experience to encompass the aspects explored in this study.

Treatment and planning for APBI requires consideration of the factors that affect the physical properties of radiotherapy in the presence of a magnetic field. The Electron Return Effect (ERE) and Electron Streaming Effect (ESE) which influence dose to skin/air/tissue interfaces all need to be understood and managed to ensure safe application of this technology [20, 21]. An evaluation of the impact of these phenomena is outside of the scope of the current study but may be examined in future work. ERE and ESE have been included in this discussion for noting as they require understanding in addition to planned dosimetry, geometric distortion, breathing and patient motion in this patient cohort.

Considering the factors that impact treatment delivery in patients receiving APBI may inform the ability to identify patients who would benefit from one position over another without requiring a scan in both positions. Body Mass Index (BMI), breast size (bra/cup), tumour bed size and specific location i.e. involved breast quadrant (upper/lower and inner/outer quadrants) information will be ascertained from this work. This will be used to inform the development of a process to streamline positioning prior to simulation, decreasing the length of simulation appointments and the number of required scans.

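### The anonymous survey records no scan order, so the stated commitment to consider order cannot be met for the position ratings and preference

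*Protocol article*

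**What the plan says.** The survey is described as anonymous in three places in the protocol article. The abstract (Methods) states: "Patient experience will be explored through completion of a short, anonymous electronic survey". Under Study design, "participants will be invited to complete a short anonymous electronic survey". The Patient experience survey section repeats it: "participants will be asked to complete a simple, short anonymous survey to assess their experience of each position". The scans get a different term: under Study design, their assessment "will be completed using the de-identified data from these scans".

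Appendix 1 prints 20 items on a four-point scale. Ten of them form five matched pairs for lying on the front and on the back: comfort (items 2 and 5), breathing (8 and 19), getting into position (13 and 17), staying still (18 and 10) and time in position (20 and 11). No printed item asks which scan came first, and none carries a study number or a patient characteristic.

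On scan order, the Positioning assessment section says: "Participants will be assigned to have either the supine or prone MRI scan first (alternating between the positions) as they are recruited". The stated purpose is to reduce bias towards either scan. It continues: "The order will also be recorded and considered in the analysis of results". No outcome is exempted.

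On later use, the abstract (Discussion) says: "Patient experience and technical considerations will be utilised to develop a tool to assist in this process". The main Discussion lists "Body Mass Index (BMI), breast size (bra/cup), tumour bed size and specific location i.e. involved breast quadrant" as information that will help streamline positioning before simulation.

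**The concern.** The ratings are given once, after both scans. Comfort, ease of keeping still and tolerance of the time spent in a position are open to fatigue, familiarity and recency. Geometric distortion, measured on a phantom with transferred contours, has little such exposure. The survey is thus an outcome for which the reason given for alternating the order applies strongly, yet its records cannot be sorted by order.

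At stake is a check on a secondary outcome. If prone were rated lower, the analyst could not see whether this held in both order groups or came mainly from those scanned prone second. The loss is permanent: order cannot be added to an anonymous form after collection unless forms are matched to appointments, which would undo the anonymity described to participants.

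**Working it through.** The article states no figure on this point, so there is nothing to reproduce. The check is a comparison of the stated elements, followed by a short calculation of the consequence.

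**Can order be attached to a survey record?**

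- Where order is held: recorded by the study for each participant (Positioning assessment).
- Where ratings are held: on a form described as anonymous (abstract, Study design, Patient experience survey).
- What could join them: a study code or an order item on the form. Neither is among the 20 printed items, and no linking step is described.

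On the text as written, the answer is no.

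**What does that cost the supine-prone comparison?**

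Let d be one respondent's supine rating minus prone rating, δ the true position difference, and g an additive effect of being scanned second rather than first, with no carry-over. Let n_S and n_P be the numbers of respondents scanned supine first and prone first.

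- Supine first: expected d = δ − g.
- Prone first: expected d = δ + g.
- All respondents pooled: expected mean d = δ + g × (n_P − n_S)/(n_P + n_S).

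The survey sample is at most 30 (Sample size estimation). The further 30 existing datasets are for distortion, positioning and dosimetry only. Alternation gives about 15 per order. The article gives no response rates, so these splits are assumptions:

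| Respondents by order | Share of g entering the pooled difference |
|---|---|
| 15 and 15 | 0/30 = 0 |
| 15 and 14 | 1/29 = about 3% |
| 15 and 10 | 5/25 = 20% |
| 12 and 8 | 4/20 = 20% |

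The size of g is unknown, so these are shares of an unknown quantity and not biases in rating points.

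**What would recording order provide?**

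- Difference between the two order-group means: (δ + g) − (δ − g) = 2g, so the order effect becomes visible.
- Simple average of the two group means: [(δ + g) + (δ − g)]/2 = δ, whatever the response split.

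Without the order field, neither quantity can be computed, and the analyst cannot tell which row of the table applies.

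**What is unaffected?**

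- McNemar's test, planned under Patient experience, needs both positions rated by the same person. One form holds both ratings, so the pairing survives.
- Distortion, distance to organs at risk, breathing motion and dosimetry come from scans, whose order is recorded.

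**The case against.** The order sentence sits under Positioning assessment, next to the MRI sequences, and the Patient experience analysis plans no order adjustment. It could be read as covering imaging only. That reading is possible, but the sentence refers to results in general, and the article does not limit it. If imaging alone is meant, the article should say so.

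The printed appendix is probably not the whole electronic form. The text promises free-text comments and open-ended questions, and the printed table shows neither. A hidden or pre-filled order field would not appear in print either. This stands as a limit on certainty: the finding concerns the article as written.

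Alternation balances order among recruits, and the survey is offered on a device at the appointment, so the article gives no reason to expect response to differ by order. This also stands. A reader might infer that the survey comparison is biased or invalid; the documents do not support that. The unbalanced splits above are assumptions, and the within-person comparison holds.

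A reader might also infer that the selection tool cannot use the survey. That goes too far. The abstract names patient experience as an input, and pooled ratings and themes can serve. The Discussion lists body size and tumour location but does not say that survey answers will be crossed with them.

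Finally, anonymity has a purpose. Items 15 and 16 ask about information and staff communication while the patient is still in the department's care, and a coded form might reduce candour.

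**Conclusion.** The point holds in a limited form. On the article's wording, scan order cannot be considered for the survey's position ratings or preference, and this cannot be repaired after collection. What is lost is the ability to check or adjust for an order effect in a secondary outcome of an exploratory pilot of up to 30 patients. The primary outcomes, dosimetry and the paired survey test are unaffected.

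Under the additive model without carry-over, the pooled comparison is free of the order effect when response is balanced, picks up about 3% of it with one missing reply, and 20% with the more uneven splits assumed above. Patient-level linkage of survey answers to BMI, breast size or tumour location is also unavailable, but no section commits to it.

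Severity is minor to moderate. It is worth acting on because the remedy is cheap and works only before the forms are collected.

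**What to change.** 1. Add one field to the anonymous electronic survey, filled by staff before the device is handed over: supine first or prone first.
2. Report the five matched item pairs, and whatever preference response is collected, by scan order as a descriptive check. With about 15 people per group the check will be imprecise and should be presented as such.
3. State that survey data inform the selection tool in aggregate only. If the sponsor wants patient-level linkage, the alternative is a coded, confidential survey with matching ethics and information wording. That is a real trade-off against candour and the anonymity promised, and this point does not require it.

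Bands for BMI or breast size on the anonymous form are not recommended: combined with scan order in at most 30 patients at one centre, they could identify individuals.

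The cost is one extra field and a very small loss of anonymity, since order alone only splits respondents into two groups of about 15. If even that is unwanted, the minimum is a sentence saying that the order analysis covers the imaging outcomes and not the survey.

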### Sample size estimation

Recruitment will cease at 12 months or when 30 patients have been recruited. This pragmatic sample size is based on the previous 12-month period of simulation appointments for this diagnosis.

Where available, existing MRI and CT datasets collected as standard of care for APBI patients will be included in the geometric distortion, positioning and dosimetry analysis aspects of the study. It is anticipated that up to an additional 30 datasets will be included in this analysis, with this de-identified data accessed under a Human Research Ethics Committee (HREC) approved waiver of consent.

### Statistical analysis

#### Positioning assessment

To compare the supine and prone positioning, categorical data will be presented as counts and frequencies, with means and standard deviations (for normally distributed data) or median and inter-quartile ranges (for non-normally distributed data) used to present continuous variables. Where appropriate, paired parametric or non-parametric tests will be applied to test for differences or equivalence between the supine and prone positions.

#### Patient experience

Quantitative survey results will be interpreted by comparison of percentage frequencies across the Likert scales. Chi Squared and Fishers Exact tests may be used to test for differences between categories, with McNemar’s test used to compare paired responses between prone and supine positioning.

Qualitative data from the open-ended survey questions will be analysed using thematic content analysis [16].

Data will be collected in a Research Electronic Data Capture (REDCap) database and/or Microsoft Excel with statistical analysis planned to be conducted using Stata version 18.0 (StataCorp, College Station, Texas, USA), with a *p*-value of < 0.05 used to indicate statistical significance.

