## Appendix 1: Participant experience survey

To help us to better understand your experience of the MRI planning scans for your radiotherapy treatment we would like to ask you some questions. You do not have to answer the questions, particularly if they make you feel uncomfortable.

Please rate the following questions and how they apply to your experience using this scale: **1** Not at all, **2** Slightly, **3** Moderately and **4** Very.

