**Table Taba:**

	Not at all	Slightly	Moderately	Very
1. I understood the procedure	1	2	3	4
2. I found the position on my tummy comfortable	1	2	3	4
3. I found the noise in the room easy to tolerate	1	2	3	4
4. I found listening to music during my scans helpful	1	2	3	4
5. I found the position on my back comfortable	1	2	3	4
6. I felt cold during my scans	1	2	3	4
7. I found the light in the room easy to tolerate	1	2	3	4
8. I found it easy to breathe lying on my tummy	1	2	3	4
9. I felt hot during my scans	1	2	3	4
10. I found it easy to stay still lying on my back	1	2	3	4
11. I found the amount of time I spent on my back easy to tolerate	1	2	3	4
12. I felt a tingling sensation during my scan	1	2	3	4
13. I found it easy to get into the position on my tummy	1	2	3	4
14. I felt calm during my scans	1	2	3	4
15. I needed more information before the procedure	1	2	3	4
16. I needed more communication from staff during the scans	1	2	3	4
17. I found it easy to get into the position on my back	1	2	3	4
18. I found it easy to stay still lying on my tummy	1	2	3	4
19.I found it easy to breathe lying on my back	1	2	3	4
20. I found the amount of time I spent on my tummy easy to tolerate	1	2	3	4

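### McNemar's test is named for paired prone/supine survey answers recorded on a 4-point ordinal scale; it fits only after a yes/no split that discards the ordering and costs power (minor).

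*Protocol article*

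**What the plan says.** All references are to the Protocol article.

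- **Instrument.** The Patient experience survey section says participants will "rate their experience of each of the positions and other common experiences of MRI scans on a Likert scale". Appendix 1 introduces the items with "Please rate the following questions and how they apply to your experience using this scale", and the scale is 1 Not at all, 2 Slightly, 3 Moderately, 4 Very. All 20 listed items use it; none is binary.
- **Pairs.** Five attributes are asked once for each position on the same form. Comfort, for example, is item 2 ("I found the position on my tummy comfortable") and item 5 ("I found the position on my back comfortable"). The others are breathing (8/19), keeping still (18/10), time in position (20/11) and getting into position (13/17). Both answers sit on one form, so the pairing survives anonymity.
- **Analysis.** Under Statistical analysis, Patient experience, the main reading is descriptive: "Quantitative survey results will be interpreted by comparison of percentage frequencies across the Likert scales". Chi-squared and Fisher's exact tests are optional for comparing categories, "with McNemar’s test used to compare paired responses between prone and supine positioning". The threshold is a p-"value of < 0.05 used to indicate statistical significance".
- **Numbers.** Under Sample size estimation, "Recruitment will cease at 12 months or when 30 patients have been recruited". The additional existing datasets are for distortion, positioning and dosimetry only, so the survey has at most 30 pairs.

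**The concern.** The one test named for the within-patient survey comparison does not match the data that the survey produces. McNemar's test compares two paired proportions and uses only patients whose answers fall on opposite sides of a single cut. On a 1-4 scale there are three possible cuts, and any movement that does not cross the chosen one counts as no difference.

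The other methods in that section do not fill the gap. Chi-squared and Fisher's exact tests ignore pairing. Percentage frequencies describe each position's answers separately, not the change within a patient.

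What is at stake is modest but real. Patient experience and position preference form a secondary aim, and the abstract says patient experience will feed a tool for choosing the position. With 30 pairs or fewer and a fixed significance threshold, a test that discards information may report no difference where an ordinal test would show one.

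**Working it through.** **1. Plan's own figure.** There is none to reproduce. The article gives no survey power, effect size, answer distribution or within-patient correlation, and its sample size is pragmatic.

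**2. How the split behaves.** Let b and c be the numbers of patients crossing the cut in each direction. Exact McNemar refers b to a Binomial(b + c, 1/2). If all crossings go one way, the two-sided p is 2 × 0.5^(b+c):
- 5 crossings: 2 × 0.5^5 = 0.0625
- 6 crossings: 2 × 0.5^6 = 0.031

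So at least 6 crossings are needed.

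Take a hypothetical result in which 10 of 30 patients answer Moderately for supine and Very for prone, and the other 20 give equal scores. At the central cut (1-2 against 3-4), b + c = 0 and McNemar's test sees nothing. At the cut 1-3 against 4, b + c = 10 and p = 2 × 0.5^10 = 0.002. A sign test on the uncut scores also gives 0.002, with no cut to choose.

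**3. Size of the loss.** Inputs from the article: n = 30 pairs, four categories, alpha 0.05. Assumptions, not from the article:
- two-sided testing;
- bivariate-normal latent scores with correlation 0, 0.3 or 0.5;
- supine answers uniform, skewed high (5/15/35/45%) or middle-heavy (10/40/40/10%).

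There were 20,000 simulated trials per setting. The latent shift was set so that the tie-corrected Wilcoxon signed-rank test on the 1-4 scores has 50% or 80% power. Relative loss = 1 − (McNemar power ÷ signed-rank power). Asymptotic McNemar is without continuity correction.

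Central cut, range over the nine combinations of distribution and correlation:

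| Signed-rank power | Exact McNemar | Relative loss | Asymptotic McNemar | Relative loss |
|---|---|---|---|---|
| 50% | 19-31% | 38-61% | 28-39% | 21-43% |
| 80% | 41-58% | 27-48% | 52-67% | 16-34% |

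Losses were taken from unrounded powers, so they can differ by a point from the rounded figures.

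At off-centre cuts the relative loss runs from 14% to 96%:
- Smallest: uniform answers, correlation 0, cut 1 against 2-4, signed-rank power 80%. Asymptotic McNemar has 69%.
- Largest: middle-heavy answers, correlation 0.5, cut 1-3 against 4, signed-rank power 80%. Exact McNemar has 3%.

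**4. Fixed-shift check** (n = 30, latent correlation 0.4, assumed answer distributions, central cut):

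| Latent shift | Signed-rank | Exact McNemar | Asymptotic McNemar |
|---|---|---|---|
| 0.5 SD | 55-57% | 25-29% | 33-38% |
| 0.7 SD | 83-85% | 51-54% | 61-64% |

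**5. Splitting the loss.** Part of the gap for exact McNemar is that test's conservatism: its type I error is about 2%, against about 5% for signed-rank. With uniform answers, correlation 0.3 and signed-rank power 50%, exact McNemar has 27% and asymptotic McNemar 35%. Of the 50 − 27 = 23-point gap, 35 − 27 = 8 points go with the exact version. The remaining 50 − 35 = 15 points are lost even with the asymptotic test.

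**6. Without collapsing.** The McNemar-Bowker symmetry test takes the whole 4×4 table but ignores category order. Its power was 5-14% where signed-rank has 50%, and 17-33% where signed-rank has 80%.

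**The case against.** Several points on the other side stand in part.

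- **Weight.** The study is an exploratory pilot with a pragmatic sample size. The preference outcome is described as a content analysis, and the percentages keep all four categories. McNemar's p-value is a supplement, and no power is claimed for it. This stands and keeps the severity low.
- **No ordinal test at all?** A reader might infer that the plan rules out an ordinal paired test for the survey. The document does not support that. The abstract's Methods allow parametric or non-parametric tests in general, according to the form of the data. But the Patient experience section names a specific test and does not carry that flexibility through. The paired non-parametric tests named in the body stand under Positioning assessment.
- **Cut point.** A reader might infer that the cut will be chosen after the data are seen. That cannot be known: a cut is a detail that an analysis plan, not shown here, could fix. The point therefore rests on the choice of test, since even a pre-stated cut discards the ordering.
- **Half the power?** A reader might infer that about half the power is lost. That is not a general figure. It is reached mainly with the exact test when signed-rank power is itself near 50%, and the article does not say which McNemar version is meant.
- **Must the answers be collapsed?** For the test as named, yes. McNemar-Bowker avoids it, but it is not named and does worse here.
- **The alternative has its own assumption.** Signed-rank treats steps along the scale as comparable in size. A tolerable/not tolerable split fixed in advance can also be a legitimate, readable target. Both are fair, and the fix allows for them.

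**Conclusion.** The point holds as a minor one. The article names a paired binary test for five item pairs that are all answered on a 4-point ordinal scale. It can be run on them only after a split that discards the ordering. With at most 30 pairs, and under the assumed distributions and correlations, the relative loss of power against signed-rank at the central cut is roughly 16-43% (asymptotic) or 27-61% (exact), and it can be larger at off-centre cuts. These sizes rest on simulation assumptions, because the article gives no effect size, answer distribution, correlation or survey power. The mismatch between test and scale does not depend on them. No primary outcome is affected.

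**What to change.** In Statistical analysis, Patient experience, replace the McNemar clause with wording such as:

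*For the five matched items (2/5, 8/19, 18/10, 20/11, 13/17), prone-minus-supine differences in the 1-4 scores will be compared with the Wilcoxon signed-rank test. The numbers of participants favouring prone, tied and favouring supine will be reported for each item. McNemar's test will be used only for a dichotomy specified before the data are seen.*

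If the sponsor does not want to treat scale steps as comparable in size, a sign test on the direction of each difference avoids that assumption at some cost in power.

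The cost is one sentence. No new data are needed, the survey is unchanged, and the test is available in the software already named.
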